**4.3.8.3 - Error Processing and Protection of Data Integrity**

It is possible that a clinician may make an error in a data collection field that is not realized until after the survey has been added to the database. In the event of such an incident, the clinician will be required to submit a corrected survey. The original erroneous survey will remain on the computer database and will not be removed until the data is concatenated into the final data collection. All corrected entries will contain coding information designating the erroneous data they supplant. This strategy will ensure integrity of the database and prevent unauthorized tampering of results. In addition, after final concatenation of survey data and tomography results, the record of any patients who did not have tomographs will be deleted from the study.

As indicated above, data collection may be by-passed on unstable victims. Such cases will be excluded from the study if the data questionnaire is not complete. Clinicians will be informed that an initially incomplete form may be completed at a later time using the same technique as described for error correction. Again, the correct and complete form will contain coded linkages to the incomplete or erroneous data record, and as stated previously all data on physiologically unstable patients will be kept and processed through a separate database. Previous experience has shown that physicians rarely enter incomplete data sets on unstable patients. In our selective cervical spine and head injury studies, we found that physicians were able to complete criteria assessments and record their findings on all unstable patients.

Additional security and data protection will be accomplished through a keyed entry system with entry codes available only to the regional study coordinators and administrators. Individuals who do not have access keys will be able to enter study data using the screen entry program, but will not have access to any additional functions on the computer.

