**3.2 - Sample size calculations.**

To be clinically reliable, the combined selective criteria must satisfy two requirements. First, intracranial injuries requiring neurosurgical intervention must never occur in blunt head trauma victims identified as risk free by the instrument. This is equivalent to requiring a 100% negative predictive value. Second, every blunt trauma victim with a significant intracranial injury must exhibit at least one of the risk criteria. This requirement implies that the sensitivity of decision instrument be 100%.

Verifying negative predictive value and sensitivity at an absolute level is not statistically possible with a finite sample size. However, it is possible to estimate limits for the true values of these proportions using exact statistical relationships. The lower confidence limit of a proportion (such as negative predictive value or sensitivity) is related to the total size of the study population. The quantitative relationship is expressed by the following equation [48]:

[figure not shown]

Where:

P_L_ = Lower confidence limit for the proportion being studied (i.e. the lower confidence limit for the negative predictive value or sensitivity of selective criteria).

X = Number of times the event of interest is observed.

N = Total number of observations.

α = Statistical confidence value (Set to 0.05).

ν_1_ = Degrees of freedom for the numerator; ν_1_ = 2 [ N - X + 1 ]

ν_2_ = Degrees of freedom for the denominator; ν_2_ = 2 X

F_α/2,ν1,ν2_ = One tailed value of the F-distribution with ν_1_ and ν_2_ degrees of freedom.

Validating a given P_L_ to a 95% level of statistical certainty implies that α = 5% (or α = 0.05). The main hypothesis of this study states that selective criteria will detect all intracranial injuries requiring neurosurgical intervention in blunt head trauma victims without missing any such injuries. Thus, for purposes of sample size calculations, for either negative predictive value or sensitivity, the event of interest (presence of one of the risk criteria) should occur with every observation. Hence, X = N.

The degrees of freedom for the numerator and denominator are then given by:

ν_1_ = Degrees of freedom for the numerator; ν_1_ = 2 [ N - X + 1 ] = 2 [ N - N + 1 ] = 2

ν_2_ = Degrees of freedom for the denominator; ν_2_ = 2 X = 2 N

The expression for the lower confidence limit then becomes:

[figure not shown]

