As discussed previously, practical concerns regarding radiographic charges and radiation health effects suggest that selective criteria will still remain cost effective and reduce mortality and morbidity even when missing 10 out of every 1,000 injuries. This implies that negative predictive value need only be verified to a 99.0% lower confidence level, or equivalently, P_L_ = 0.99. Substituting this value in the lower confidence limit equation yields the following algebraic equation for intracranial injury population size N;

[figure not shown]

The numerical solution to this equation is N = 368. Thus, to confirm that the decision instrument has a negative predictive value of at least 99.0%, the study must enroll 368 head injury victims who have none of the risk criteria, and none of whom have intracranial injuries requiring neurosurgical intervention. Since approximately 10% of head trauma victims are free of the risk criteria, this derivation would require a population of 3,680 head trauma victims. Unfortunately, confirming that the instrument has a 99.0% sensitivity requires studying 368 intracranial *injury* victims. Surgically significant intracranial injuries occur in only 1.2% to 1.4% of head trauma cases. Assuming a serious injury prevalence of 1.2% implies that this study will need to prospectively evaluate 31,000 blunt head injury victims. Consequently, study size is driven by the requirements of sensitivity.

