Because computer generated requests will be required for all emergency department head tomographs, patients who present with non-traumatic indications may be enrolled in the study. Physicians will be required to indicate the non-traumatic nature of these evaluations. To assure compliance with the methods of this proposal, clinicians will still be required to enter relevant study information. This information will be retained in a separate database, and will be analyzed separately from data on blunt head injury victims. This information may be useful in developing selective indications for non-traumatic computed head tomography. However, this information is not relevant to the hypotheses being tested in this study.

Imaging requests may be generated prior to complete data entry in physiologically unstable patients. Clinicians will ultimately complete data entry in these patients, but complete data entry may occur after computed head tomographs have been reviewed. In such cases, the data entry for the case will document the physiologic instability and non-concurrent nature of the data collection. In our previous study, clinicians classified 8.7% of patients as unstable (including 17.5% of patients with intracranial injuries), but were able to complete assessments on all patients. In this regard, the study protocol allowed clinicians to provide expeditious care to even the most severely injured patients, while having a negligible impact on data collection.

Data will be collected on all blunt head injury victims entered into the study. Inclusion will not depend on age, sex, race or ethnic origin. Specific information regarding race will be collected to determine what effect, if any, race may have in evaluating patients for risk of injury. Demographic analyses will be performed on age and sex data. Study sites (Appendix A) have been selected to represent a broad spectrum of medical environments. These sites are expected to enroll a diverse population containing all races and both sexes. All sub-populations will be represented in the study in the same proportions as they present with blunt head injuries.

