**4.3.7 - Data Analysis**

The primary outcome for the study is the point measure and associated 95% confidence interval for the sensitivity of the decision instrument in identifying patients who require neurosurgical intervention. Additional operator characteristics of interest for this population include the negative predictive value and specificity. Secondary outcomes include the sensitivity, negative predictive value and specificity of the instrument in detecting patients who harbor clinically significant intracranial injuries as described by the criteria defining positive CT imaging (see 4.3.5.1.2 - Injury Diagnosis above). A further secondary goal of the study is to determine and compare the operator characteristics of both the NEXUS head CT instrument, as well as both forms (“high risk” and “medium risk”) of the Canadian head CT instrument, among patients who meet the inclusion and exclusion characteristics for classification by the Canadian rules.

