**4.3.7.1.2 - Unstable patients**

Unstable patients make up a small minority of minor blunt head injury victims. The exact proportion varies from hospital to hospital. This makes it impossible to accurately estimate how many of these patients may be entered into the study. Because physicians may defer complete data entry on unstable patients, it is possible that final records for some of these patients might be incomplete. However, in our selective cervical spine and previous head injury studies we found that less than 10% of the study patients were classified as unstable, and all of these patients had complete criteria assessments. Thus, missing data from unstable patients is unlikely to be a significant problem in this validation study. In addition, physicians will be required to supply a minimal amount of demographic information on these patients prior to tomographic request generation, and are requested (and required by protocol) to complete data entry on all patients (even though this data entry may be non-concurrent). Records containing incomplete data will not be used in validating the decision instrument. These entries *will* be used in descriptive analyses on the demographics and injuries patterns associated with mild head trauma. Cases missing tomographic reports and information regarding the need for neurosurgical intervention will be deleted from the study.

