**4.3.9 - Difficulties and Limitations**

**4.3.9.1 - Sensitivity and Negative Predictive Value**

Errors in the estimation of sensitivity and negative predictive value of the screening strategy could bias the internal validity of this study. Bias in these estimates could occur through misclassification of patient injury status, or if doctors change their answers after tomographic review and diagnosis. The diagnosis of injury will be based on the final tomographic interpretation and need for neurosurgical intervention, and in the majority of patients, absence of injury will be determined by a single computed tomographic series. Thus, true sensitivity will depend on both the sensitivity of selective criteria as well as the negative predictive value of standard tomographic imaging. However, it is not the purpose of this study to determine the optimal method of radiographic evaluation. If an injury is missed on standard computed tomography, the method of patient selection is irrelevant since such cases would be misidentified even if tomography were performed on all patients. Thus, the measured sensitivity is the parameter of interest. Bias due to alteration of data forms will be eliminated by requiring data to be entered into the computer prior to generation of tomography requests. This leaves the potential for misrepresentation of data in critically ill patients, but these patients will in general be excluded from the mild head injury status by virtue of their critical illness. Thus bias in sensitivity due to data alterations should be insignificant.

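### Criteria can be corrected or first completed after the CT is read, yet the protocol calls this bias eliminated and leans on an exclusion of critically ill patients that no entry rule makes

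*Protocol*

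**What the plan says.** The primary outcome (Protocol, 4.3.7) is the "sensitivity of the decision instrument in identifying patients who require neurosurgical intervention", with an exact 95% interval. Three sets of statements bear on when the criteria are recorded.

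- **Corrections.** Under 4.3.8.3, when an error is found after the survey has entered the database, "In the event of such an incident, the clinician will be required to submit a corrected survey". The corrected entry is coded to the data it replaces, and the original is kept only until final concatenation. Section 4.3.6 says a site cannot alter a completed form, but refers error correction to this same route.
- **Late entry.** For physiologically unstable patients, 4.3.2.1 says "complete data entry may occur after computed head tomographs have been reviewed", with the record marked as non-concurrent. Section 4.3.8.3 lets an incomplete form be completed later. Section 4.3.7.1.2 says "Records containing incomplete data will not be used in validating the decision instrument".
- **Bias.** Section 4.3.9.1 says "Bias due to alteration of data forms will be eliminated by requiring data to be entered into the computer" before the CT request is generated. It then concedes that data on critically ill patients could be misrepresented, sets this aside because such patients will in general fall outside mild head injury, and concludes that the bias should be insignificant.

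Section 4.3.8.3 also says that "all data on physiologically unstable patients will be kept and processed through a separate database", and presents this as something stated before.

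**The concern.** Entry before the CT request protects against bias only if the entry made then is the one analysed. Here a later entry may take its place, at a time when the clinician may know the scan result. A clinician who learns of a serious bleed has reason to look again at a form with every criterion marked absent. If one No becomes Yes, a false negative becomes a true positive. No bad intent is needed: honest reconsideration is more likely where the instrument missed an injury, so the error raises sensitivity.

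The treatment of unstable patients matters for the same reason. They are the group for whom late entry is expressly allowed, and 4.3.9.1 relies on their being largely absent. If they are present, that argument fails. If they are absent, the study is missing a share of the cases on which the sample size rests.

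**Working it through.** **Timing of corrections.** For stable patients the CT request is issued only after the form is complete (4.2, 4.3.2.1). Any correction to an entered form therefore follows the request. It may come before or after the result; nothing in 4.3.8.3 draws that line.

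**Status of unstable patients.** The statements are:

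1. 4.3.7.1.2 and 4.3.8.3 remove unstable records only if incomplete, so late but complete ones remain.
2. 4.3.8.3 sends all unstable data to a separate database, as already stated. The only separate database described earlier (4.3.2.1) is for scans done for non-traumatic reasons.
3. 4.3.9.1 says critically ill patients will in general be excluded. No entry rule does this, and 4.3.2.1 collects data on all blunt head injury victims entered.

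**The plan's own figure.** Section 3.2 sets α = 0.05, with α/2 in the tail, and says "negative predictive value need only be verified to a 99.0% lower confidence level"; it then applies the same limit to sensitivity. With no misses (X = N) the exact lower limit reduces to

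P_L = (α/2)^(1/N) = 0.025^(1/N).

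Setting P_L = 0.99 gives N = ln(0.025)/ln(0.99) = 367.04, rounded up to 368. At 368 the limit is 0.99003; at 367 it is 0.989999. At 1.2% prevalence, 368/0.012 = 30,667, which the protocol gives as 31,000. Both figures reproduce.

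**Effect of one changed answer** (exact lower limits):

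| Detected | Lower limit |
|---|---|
| 368/368 | 99.00% |
| 367/368 | 98.50% |
| 366/368 | 98.05% |

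**How many cases could be entered late.** Section 4.3.2.1 reports that in the earlier study 8.7% of all patients, and 17.5% of those with intracranial injury, were unstable. No share is given for neurosurgical cases, so the table applies these two figures and an assumed 30%. It further assumes that every unstable case is entered late, that all count toward the 368, and that none is missed.

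| Unstable share | Late cases of 368 | Pre-CT cases | Lower limit, pre-CT cases |
|---|---|---|---|
| 8.7% | 32 | 336 | 98.91% |
| 17.5% | 64 | 304 | 98.79% |
| 30% | 110 | 258 | 98.58% |

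For example, 0.175 × 368 = 64.4; 368 − 64 = 304; 0.025^(1/304) = 0.9879.

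If instead enrolment ran until 368 pre-CT cases were reached, the 17.5% share would need 368/0.825 = 446.1, so 447 cases, or 447/0.012 = 37,250 patients.

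**The case against.** Several points on the other side stand.

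- No sentence says outright that corrected or late records enter the primary analysis. It follows from the correction replacing the original and from only incomplete records being barred. A statistical analysis plan could name the version to be analysed. It could not make the claim in 4.3.9.1 consistent with 4.3.8.3.
- Section 4.3.9.1 does admit a residual risk in critically ill patients. The fault lies in the reason given for dismissing it.
- The operative rules on unstable records agree with each other: complete ones stay, incomplete ones go. Processing in a separate database need not mean exclusion.
- Safeguards exist. Clinicians are to form their answers before viewing the scan (4.2), late entry is flagged (4.3.2.1) and corrections are linked to what they replace (4.3.8.3). But unrecorded answers cannot be checked, and the protocol ties no analysis rule to the flags or links.
- A criterion that cannot be assessed already makes the patient positive (4.3.3). Late entry can rescue a miss only where every criterion would have been assessed and found absent, which limits the number of unstable cases at risk.
- The late-entering clinician knows the CT result, not the seven-day outcome. The two are close, however, because intervention is sought in the records of CT-positive patients (4.3.5.1.2).

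A reader might infer that 64 of the 368 cases are contaminated, or that the limit will fall to 98.79%. The documents support neither. They give no rate of late entry or correction, and late entry is permitted, not expected in every case. Under 4.3.10.3 collection runs to 368 neurosurgical cases, so if excluded cases were not counted the result would be longer enrolment and not a lower limit.

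**Conclusion.** The concern holds as a conflict between the protocol's bias claim and its own data rules. The claim that alteration bias is eliminated does not survive the correction route, and the conclusion that it is insignificant rests on an exclusion the protocol does not make. The reference to an earlier statement on a separate database for unstable patients has no match.

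The size is set by the zero-miss target: a single answer reversed after the CT is known moves the lower limit from 98.50% to 99.00% and decides whether the instrument is validated. This needs only that such a reversal be allowed, which it is. It is not evidence that reversals will occur. The figure of about 64 late-entered cases (32 to 110 over the range shown) is conditional on the two assumptions stated with it: transfer of the share from intracranial injury, and late entry of every unstable case.

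**What to change.** 1. In 4.3.7 and 4.3.8.3, state that for records complete before the CT result, the primary analysis uses the last version entered before that result. Later corrections appear only in a supplementary analysis.
2. Keep every survey version with its entry time, and do not remove originals at concatenation. Settle this before concatenation begins, since 4.3.8.3 allows removal then.
3. Reconcile 4.3.2.1, 4.3.7.1.2, 4.3.8.3 and 4.3.9.1 into one rule: complete unstable records are in the study, flagged as non-concurrent where they are. Drop or explain the separate-database sentence, and drop the statement on general exclusion.
4. Report sensitivity with its exact limit twice, for all complete records and for records entered before the CT result. State that the 99.0% claim must also be judged on the second set, and give the limit actually attainable there (for example 98.79% if 304 cases qualify with none missed).
5. In 4.3.9.1, replace the words claiming elimination and insignificance with a statement of the remaining risk and how it will be shown.

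The cost is protocol wording, one further table, and storage of survey-entry and CT-result times, which neither 4.3.3 nor the Appendix B form lists. Some genuine late corrections will not be used in the primary analysis. The pre-CT set will under-represent unstable patients, which is why both estimates should be shown.

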**4.3.8.4 - Equipment Failures**

Data collection at individual hospitals will be suspended in the event of computer system failure. If such a failure should occur, any retrievable data will be transmitted to UCLA for concatenation at the earliest possible opportunity. Site liaisons will be responsible for identifying equipment failures and initiating appropriate corrective action. During equipment failures, the affected institution will be allowed to perform data collection using pre-printed paper survey forms and will need to obtain radiographic imaging using their pre-study protocols. Information collected on printed forms will be entered into the study database at the earliest possible opportunity.

**4.3.8.5 - Study Site Termination**

If an individual study site should withdraw from the study, or otherwise be unable to participate in data collection, the site will be removed from the study and all collected data retrieved. A new site will then be selected from a list of alternative hospitals. The site will be chosen on the basis of geographical proximity, hospital type (community vs. university vs. county) and patient population.

**4.3.9 - Difficulties and Limitations**

**4.3.9.1 - Sensitivity and Negative Predictive Value**

Errors in the estimation of sensitivity and negative predictive value of the screening strategy could bias the internal validity of this study. Bias in these estimates could occur through misclassification of patient injury status, or if doctors change their answers after tomographic review and diagnosis. The diagnosis of injury will be based on the final tomographic interpretation and need for neurosurgical intervention, and in the majority of patients, absence of injury will be determined by a single computed tomographic series. Thus, true sensitivity will depend on both the sensitivity of selective criteria as well as the negative predictive value of standard tomographic imaging. However, it is not the purpose of this study to determine the optimal method of radiographic evaluation. If an injury is missed on standard computed tomography, the method of patient selection is irrelevant since such cases would be misidentified even if tomography were performed on all patients. Thus, the measured sensitivity is the parameter of interest. Bias due to alteration of data forms will be eliminated by requiring data to be entered into the computer prior to generation of tomography requests. This leaves the potential for misrepresentation of data in critically ill patients, but these patients will in general be excluded from the mild head injury status by virtue of their critical illness. Thus bias in sensitivity due to data alterations should be insignificant.

Errors in sensitivity and negative predictive value may also occur through biased enrollment. Practical concerns, such as cognitive impairment among head injury victims, make it impossible to obtain informed consent on all patients. To eliminate the potential for selection bias we instituted methodologies that allow us to conduct an observational study under a waiver of informed consent. This approach ensures that we will enroll all patients who undergo tomographic scanning (including those most likely to have intracranial injuries), but limits our ability to obtain CT scans on all blunt head injury victims. In this process, our methodology introduces the potential for workup bias. However, errors would occur only if a patient with a significant head injury exhibited none of our study criteria *and* was not selected for tomographic scanning. Such a case would represent an undetected false-negative event; the decision instrument would fail, and we would be unaware of the failure. Although such an event is theoretically possible, available studies indicate that essentially all significant head injury victims exhibit some symptomatology. As noted in our background discussion, there are no case reports describing significant intracranial injuries in an individual who does not exhibit at least one of our initial screening criteria. Furthermore, in our derivation study, we obtained follow-up evaluations on 1,266 patients who did not undergo computed tomography during their initial presentations. These evaluations revealed that a small minority of these patients ultimately received cranial imaging. However, none of these cases required hospitalization or neurosurgical intervention, and there were no cases of missed intracranial injuries or death among this cohort [65]. Thus, the potential for work-up bias is a theoretical possibility, but is of less practical concern. Furthermore, we will screen patient revisits and inpatient neurosurgical trauma admissions to identify patients who might produce such bias. Finally, as mentioned previously, we will obtain criteria evaluations and contact information for 368 consecutive blunt head trauma patients who present to the Ronald Reagan UCLA Medical Center and do not undergo emergent tomographic head imaging during their initial evaluation. We will contact these patients, or their family, three months after their enrollment to determine whether they were eventually diagnosed as having a significant intracranial injury or required hospitalization or neurosurgical intervention. The survey form used in these follow-up assessments is similar to the one used in the previous head injury study, and a copy of the survey form is presented in Appendix - D. Based on our previous experience, we estimate that we will be able to complete survey interviews on approximately 98% of the enrolled patients [65]. This process will effectively screen a large subset of patients who are not otherwise enrolled in the study, and will allow us to not only detect workup bias, but also estimate its magnitude. Thus, although we cannot completely eradicate the potential for measurement bias, our methodology makes it unlikely that it will be present without our knowledge.
